#### **8-8-2 Statistical analysis**

The statistical analyses will be performed by the Oscar Lambret Center Methodology and Biostatistics Unit (*Unité de Méthodologie et de Biostatistique*, UMB).

The study populations will be as follows:

- The descriptive analysis of baseline characteristics will be performed on the patient population enrolled in the study.
- The descriptive analysis of the procedure, disease, morbidity, and satisfaction questionnaire will be performed on the patient population who underwent radical fimbriectomy.

- The analysis of cumulative incidence of pelvic cancer, breast cancer, and secondary oophorectomy will be performed on the patient population who underwent surgery and excluding patients with invasive cancer or STIC on the fimbriectomy specimen.
- The analysis of secondary oophorectomy complications will be performed on the patient population who underwent oophorectomy secondary to the fimbriectomy.

The statistical analysis of baseline characteristics, procedure, and disease will be essentially descriptive in nature and will be presented in summary tables including the number of missing data. Continuous variables will be summarized by median and extreme values, and mean and standard deviation if warranted. Categorical variables will be presented as contingency tables (absolute frequency and percentage of each modality).

The inclusion and exclusion criteria will be verified from the data recorded in the case report forms. Any protocol deviations will be detailed, as well as the causes of ineligibility and non-evaluability.

The cumulative incidences of pelvic cancer, breast cancer, and secondary oophorectomy will be estimated by the competitive risk method (Kalbfleish [*sic*: Kalbfleisch] and Prentice), as defined in section 8.7 (endpoints).

In secondary analysis, cumulative incidences of pelvic cancer and breast cancer will be estimated based on age reached.

Early postoperative morbidity (assessed by Clavien-Dindo scale within 30 days post-operatively) and late postoperative morbidity (occurring in a period of more than 30 days and assessed by NCI-CTCAE) will be described by type of adverse event, grade and relationship to the fimbriectomy or secondary oophorectomy. The type of adverse event (AE) will be described by SOC (System Organ Class) and PTname (Preferred Term) of the medDRA medical dictionary. The maximum grades observed by type of AE will be described in tabular form: number and frequency. Serious adverse events (SAE) will be described.

Each item of the satisfaction questionnaire will be described by its median, extreme values, mean and standard deviation.

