#### ***All criteria are required for inclusion:***

- Women over 35 years of age
- After completion of the pregnancy
- BRCA 1 or 2 mutation, or family breast/ovarian documented by genealogy
- Not ready for bilateral adnexectomy (procedure that will always be routinely offered 1st)
- Involvement or not of breast cancer
- Affiliated with a social security plan

- Informed consent and signed by the patient prior to implementation of any study-specific procedures

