### 8-5 Study withdrawal criteria

Patients will be followed until menopause (no periods for more than 1 year).

The criteria for withdrawal from the study are:

- Post-fimbriectomy oophorectomy (patients will be followed 1 month post-procedure for complications)
- Patient decision
- Patient lost to follow-up
- Patient death

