### ***8-7-5 Postoperative complications***

Morbidity will be assessed:

- up to 30 days post-procedure according to the Clavien-Dindo classification [2009]
- and beyond this time (until confirmation of menopause for patients who have not had a secondary oophorectomy, or up to one month after secondary oophorectomy) according to the NCI-CTCAE v4.0 grading scale.

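### Late morbidity is summarised only as a crude percentage although follow-up length differs greatly between women; for slowly accruing events a rate per woman-year should stand beside it

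*Protocol*

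**What the plan says.** All references are to the protocol.

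- **Collection window.** Section 8-7-5 grades morbidity by Clavien-Dindo up to day 30. After that it uses NCI-CTCAE, "until confirmation of menopause for patients who have not had a secondary oophorectomy, or up to one month after secondary oophorectomy". Section 8-5 agrees: "Patients will be followed until menopause (no periods for more than 1 year"), and one of the withdrawal criteria is "Post-fimbriectomy oophorectomy (patients will be followed 1 month post-procedure for complications").
- **Entry.** Section 8-2 admits "Women over 35 years of age" and states no upper age limit. Section 8-3 excludes postmenopausal women.
- **Denominator (8-8-2).** "The descriptive analysis of the procedure, disease, morbidity, and satisfaction questionnaire will be performed on the patient population who underwent radical fimbriectomy".
- **Summary (8-8-2).** Early and late morbidity "will be described by type of adverse event, grade and relationship to the fimbriectomy or secondary oophorectomy". The tabulation is then fixed: "The maximum grades observed by type of AE will be described in tabular form: number and frequency". The synopsis says the same. Neither attaches a time point, person-time or follow-up duration to the late-event figures.
- **Other outcomes in the same section.** "The cumulative incidences of pelvic cancer, breast cancer, and secondary oophorectomy will be estimated by the competitive risk method". Late adverse events are not on that list.

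**The concern.** The early table has a fixed 30-day window, so its percentage means the same for every woman. The late table does not. A woman who has her ovaries removed one year after fimbriectomy and a woman followed for twelve years without an event both count as one woman without an event.

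Oophorectomy nearer the age of menopause is the intended second step of the strategy (6-2, 8-6-3), so one of the things that closes the collection window is part of the treatment plan. The late events that 8-6-3 asks gynecologists to look for include menstrual disorders, hot flashes and vaginal dryness, which can appear years after surgery.

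Morbidity of the operation is the first secondary objective listed in 7-2. For slowly accruing events, a percentage with no time reference is hard to interpret and hard to set beside another series with a different follow-up.

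**Working it through.** The protocol states no figure for late morbidity, so there is nothing to reproduce. The check asks how far the crude percentage moves with oophorectomy uptake when the event rate is held fixed.

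**Range of follow-up.** From the protocol: entry over 35, premenopausal, followed to menopause; recruitment ended October 2014 and study end is projected for August 2034, about 19.8 years later. Windows from months to more than a decade are an inference, but these rules allow them.

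**Assumptions (none given in the protocol).** Constant late-event hazard *a* of 1%, 2% or 5% per year; constant oophorectomy hazard *o* of 0 to 20% per year; time *T* from surgery to menopause. The first 30 days and the extra month after oophorectomy are ignored.

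**Formula.** Crude proportion with an event before collection ends = a/(a+o) × (1 − exp(−(a+o)T)).

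**1. Fixed T = 10 years, a = 2%**
- o = 0: 1 − exp(−0.2) = 18.1%
- o = 5%: 0.02/0.07 × (1 − exp(−0.7)) = 14.4%
- o = 10%: 0.02/0.12 × (1 − exp(−1.2)) = 11.6%
- o = 20%: 0.02/0.22 × (1 − exp(−2.2)) = 8.1%

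From 10% to 20% uptake the ratio is 11.6/8.1 = 1.4. The effect grows with *T*: from no oophorectomy to 20% per year, the figure goes from 9.5% to 6.1% at T = 5 and from 25.9% to 8.8% at T = 15.

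**2. Mixed entry ages.** Age at surgery uniform from 36 to 48 and menopause at 51, so *T* is uniform from 3 to 15 years and the formula is averaged over *T*.

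| Uptake per year | Follow-up, median (10th–90th percentile), years | Crude %, a = 2% | Crude %, a = 5% | First events per 100 woman-years at risk |
|---|---|---|---|---|
| 5% | 6.6 (2.1–12.7) | 12.9 | 28.4 | 2.0 and 5.0 |
| 10% | 5.1 (1.1–11.3) | 10.5 | 23.5 | 2.0 and 5.0 |
| 20% | 3.3 (0.5–8.5) | 7.4 | 17.0 | 2.0 and 5.0 |

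The ratio from 5% to 20% uptake is 12.9/7.4 or 28.4/17.0, about 1.7. From 10% to 20% it is 10.5/7.4 or 23.5/17.0, about 1.4. The woman-year rate does not move.

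**3. Harm still drives the figure.** With o = 10% and T = 10, hazards of 1%, 2% and 5% per year give 6.1%, 11.6% and 25.9%.

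**4. Early harm.** Suppose 10% of women are ever affected, with onset at rate *r* = 1 per year and T = 10. The crude figure is 0.10 × r/(r+o) × (1 − exp(−(r+o)T)): 10.0% with no oophorectomy, 9.1% at 10% per year and 8.3% at 20% per year.

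**5. Cumulative incidence with oophorectomy as a competing event.** For a = 5%, the 5-year value a/(a+o) × (1 − exp(−5(a+o))) is 19.7%, 17.6% and 14.3% at uptake of 5%, 10% and 20%. That is still a 19.7/14.3 = 1.4-fold fall. The 1-year values are 4.8%, 4.6% and 4.4%.

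**The case against.** **The plan is conventional and the stakes are limited.** Maximum grade by preferred term is a standard table. The endpoint is descriptive in a single-arm study: no test or stopping rule uses it, since the rules in 8-8-1 count pelvic tumors only. Exposure-adjusted rates could be added in a statistical analysis plan, and 8-8-2 does not exclude them. All of this stands and sets the weight of the point. It does not remove it, because 8-8-2 names a summary that fits the late collection window poorly.

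**The size depends on an assumed shape.** Section 8-7-5-3 limits specific operative morbidity to bleeding, with a theoretical later risk of induced menopause. If harm appears early, step 4 shows little distortion. This also stands: the point concerns slowly accruing events, not late morbidity as a whole.

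**Stronger readings that the protocol does not support.**
- A reader might infer that the percentage tracks oophorectomy uptake rather than surgical harm. Step 3 shows that it moves with both.
- A reader might infer that all safety collection stops at menopause or oophorectomy. Section 8-7-5-6 requires serious events reasonably related to the research to be reported after day 30 with no time limit.
- A reader might infer that operative safety cannot be compared with other series. The 30-day table has a fixed window and is unaffected.
- A reader might infer that complications of secondary oophorectomy are mixed in without provision. Section 8-8-2 gives them their own population, and 8-7-4 sets a one-month window.

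**Conclusion.** The point holds in a limited form. The crude percentage for late events has no time reference, and for events that accrue over years it depends on follow-up length and oophorectomy uptake as well as on harm. Under assumed constant hazards and the entry-age mix in the table, the shift is about 1.4-fold between 10% and 20% uptake per year and about 1.7-fold between 5% and 20%. It is smaller when menopause is near or harm is early, and larger when menopause is far off. The hazards, uptake rates and ages are all assumptions. No between-arm comparison or decision rule is affected. This is a cheap improvement, not an error that threatens the trial's conclusions.

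**What to change.** In 8-8-2 and the synopsis:

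1. Keep the crude table of maximum grades, for early and late events.
2. For late events, add the duration of follow-up (median and range) and the number of first events per 100 woman-years by event type. Count woman-years from day 31 to the end of each woman's collection window and, for a woman who has the event, stop at its onset.
3. Optionally, add the cumulative incidence at fixed early times, for example 1, 3 and 5 years, by the competing-risk method already planned. State that with oophorectomy as a competing event it still falls as uptake rises (step 5), so it supplies a time reference but does not remove the dependence.

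The woman-year rate is free of uptake only while the hazard is roughly constant, which is one reason to keep the crude table beside it. No change is needed for complications of secondary oophorectomy.

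The cost is a few lines of text and one table, since 8-7-5-1 already records the onset date of each adverse event. The downside is imprecise rates for rare event types and a little more analysis.

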### **8-8-3 Data Management**

Data management will be performed in collaboration with the Northwest Cancer Center Data Processing Center (CTD (*Centre de traitement des données* [Data Processing Center])-CNO (*Cancéropôle nord-ouest* [Northwest Cancer Center]), approved by the INCa. A study-specific database will be created using the Capture System (CLINSIGHT) and tested and validated prior to entry.

A data validation plan will be developed and will describe in detail the controls to be executed for each variable as well as the list of allowable obvious corrections. The data will be monitored by the data management team using error messages from validation programs. The obvious errors will be corrected. The other errors, omissions or inconsistencies will be mentioned on the correction request forms, which

will be sent to the study investigator for resolution. The corrections will be included by the Clinical Research Associate Monitor (CRA-M) in the database.

#### Special case

The data related to benign histological abnormalities and satisfaction questionnaire will be collected in an Excel spreadsheet, and hosted securely by the Methodology and Biostatistics Unit, before being included in the final analysis.

The database will be frozen after final quality control and then exported to STATA statistical software using an automated and validated procedure.

## 9 CONDUCT OF THE STUDY

### 9-1 Process flow

#### **9.1.1 Patient enrollment**

An enrollment request form will be completed by the investigator to ensure that the patient meets ALL screening criteria. The investigator must give the information letter to the patient and have the document signed (consent) allowing the subject to express his/her willingness. PRIOR TO SURGERY, the investigator must fax the enrollment request form to the Study Coordination Center:

***Integrated Clinical Research Unit/Promotion Unit  
of the Oscar Lambret Center – Lille***

[contact]

After verification of all screening criteria, an identification number will be assigned. A confirmation of enrollment will be sent to the study doctor.

#### **9.1.2 Surgery: fimbriectomy**

The surgical procedure consists of a laparoscopic bilateral radical fimbriectomy. The principle is to resect almost all of the tubes, from the uterine horn (at the level of the uterus because carcinomas develop on the distal part) to the fimbriae, by resecting the part of the ovary adjacent to the ovarian fimbriae (which adhere to the ovary). This associated ovarian resection, which justifies the term "radical", has 2 objectives:

- The first, real, is to ensure resection of the entire fallopian tube fimbrial end and tubal-ovarian adhesion.
- The second is to resect the fimbria/ovarian junction, the area that appears most sensitive to the development of serous lesions [Auersberg 2010; Seidman 2010] and, more hypothetical, to remove this transitional epithelium from which Brenner tumors and some mucinous carcinomas would develop [Kurman 2010].

This leaves at least 4/5 of the initial ovarian volume in place on each side. The ovaries remain vascularized by their respective utero-ovarian pedicles. The procedure is performed laparoscopically.

In accordance with national guidance regarding adnexal prophylactic surgery (August 2009 on [www.e-cancer.fr](http://www.e-cancer.fr)), peritoneal cytology and systematic peritoneal biopsies (excluding suspicious lesion) will not be performed.

The laparoscopy is set up as for a classic bilateral adnexectomy:

- Ventilated intubated patient with empty bladder and stomach, supine, arms along the body.
- 15 to 20° Trendelenburg position applied after insertion of the optic.

Pneumoperitoneum performed according to the patients by puncture in the upper left quadrant of the abdomen or by open laparoscopy. Blind umbilical punctures should be avoided in favor of left subcostal puncture.

- Four trocars are put in place:
  - 2 x 10 mm trocars, 1 umbilical for the optic and 1 medial suprapubic for instruments and protected specimen extraction
  - and 2 x 5 mm trocars placed in the iliac fossae outside the epigastric pedicles for the instruments. This can also be done using the single [site] umbilical trocar technology (cosmetic advantage).
  - **Variant:** The use of a single umbilical trocar (Gelpoint® Applied Med type) is possible. With this device, specimens can be extracted directly through the umbilicus, and through the gel, since the wall is protected.

After careful exploration of the abdominopelvic cavity, and in the absence of a suspicious abnormality, the fimbriectomy itself is performed:

- It begins by separating the tube from the uterus, flush with it.
- The bipolar coagulation of the tube will prevent any bleeding.
- The underlying utero-ovarian pedicle should not be coagulated because it will become the only vascular collateral of the part of the ovary left in place.
- The mesosalpinx sectioning is then performed with scissors as close as possible to the interstitial portion of the tube so as not to injure the vascular arch over the ovary.
- At the fimbrial end of fimbriae, the ovary is gently grasped and its section proceeds beyond the insertion of the utero-ovarian ligament.
- During this procedure, all or part of the pelvic infundibular pedicle must be sectioned after hemostasis.

The procedure is of course bilateral.

In case of a single adnexa (e.g., history of salpingectomy for ectopic pregnancy), the procedure will be unilateral without the need to resect the contralateral isolated ovary (unless abnormal).

There is apparently no difference in technical difficulty on one side or the other, except for the need, on the left, as with conventional adnexectomy, to pre-release possible adhesions between the sigmoid colon and the adnexa.

A biopsy will be performed if a pelvic macroscopic abnormality is discovered.

The extraction of the fimbriectomy specimens will be carried out in separate endoscopic bags (specifying which side is sampled).

We conducted a comparative study of the different means of sectioning and ovarian hemostasis [Leblanc 2011]:

- the use of cold scissors with additional non-routine bipolar hemostasis or the use of EndoGIA® 45mm Forceps (Autosuture Tyco Healthcare France) vascular staples are the most effective methods for hemostasis and tissue alterations.
- The bipolar-scissor combination has our preference over EndoGIA® that is less comfortable to use (especially if single trocar) and is of a significant cost.
- Note: A video explaining the procedure will be sent to the participating sites. One of the surgeons at the Coordinating Center will also be available for any on-site assistance if necessary.

## 9-2 Histopathology

The detection of early occult lesions within prophylactic bilateral adnexectomies performed in BRCA mutated women requires detailed and rigorous sampling of these adnexas. This meticulous approach shows that these small lesions, often less than 1 mm in size, are more commonly located in the tubal infundibulum rather than in the ovary.

The pathological study of operative specimens should optimize the possibility of detecting early carcinoma.

The tubes and ovarian portions covered by the tube should be studied in their entirety with a more careful study of the fibrial end. The ideal dissection protocol should optimize visualization of the mucous membrane of the fibrial end of the tube and surface epithelium of the ovary.

## 9-3 "Selectionning [*sic*: Sectioning] and Extensively Examining the FIMbria" protocol (SEE-FIM)

The surgical specimens are sent fresh to the pathology laboratory of each participating site.

### 9.3.1 Macroscopic management

Tubes: after separating the fimbrial end and the infundibulum from the ampulla and isthmus①, the fimbrial end and the infundibulum are cut longitudinally② (in the direction of the length of the fimbrial end fimbriae). The sections are preferably placed in 2 cassettes to spread the tube fimbriae properly. The rest of the tube is cut into sections perpendicular to its axis③.

Ovarian portions covered by the tube: each ovary fragment is sectioned perpendicular to its longitudinal axis④.

To enable detection of lesions of 1 millimeter, the cut sections should not exceed, if possible, a thickness of 2 to 3 mm. Under these conditions, each adnexa represents approximately 10 to 15 cassettes.

[figure not shown]

### 9.3.2 Histological management

- For each block of tube, 1 ribbon of 7 representative sections is made.
- Standard Hematein-Phloxin-Safran (HPS) staining is performed routinely (and first-line) as well as first-line immunohistochemistry with anti-p53 and anti-ki67 antibodies.
- The other 4 sections are kept in reserve.
- The performance of first-line serial sections is unnecessary: these will be requested later by the pathologist in case of diagnostic doubt.
- For each block of ovary, 1 ribbon of 7 sections is made.
- These ribbons are stored after HPS staining on one of the sections of each ribbon.

The immunohistochemical study is not routine and may later be requested by the pathologist based on histological findings on the HPS.

## 9-4 Subsequent processing

### 9.4.1 Incidental finding of invasive cancer

In case of incidental discovery of invasive ovarian or peritoneal tubal carcinoma, a further procedure will be scheduled that will follow the surgical and medical management rules for invasive ovarian carcinoma developed by the National Cancer Institute guidelines team in 2009 (documents available at: [www.e-cancer.fr](http://www.e-cancer.fr)).

Otherwise, pelvic monitoring is started, the procedures of which are described below.

#### **9.4.2 Secondary bilateral oophorectomy**

Secondary bilateral oophorectomy will be performed solely after release of potential periovarian adhesions by coagulation and sectioning of the pedicle and utero-ovarian ligament. The broad ligament of the uterus approach (through opening of the peritoneum along the external iliac pedicle) may be necessary in case of adhesions to this pedicle or if the infundibulopelvic ligament has been preserved. In these cases, checking the position of the ureter will avoid subsequent complications. They will also be extracted through endoscopic bags.

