### **8-6-3 Follow-up report**

The primary objective of radical fimbriectomy is to reduce the risk of serous pelvic carcinoma (ovarian or peritoneal) with a predominant tubal origin, while awaiting definitive castration.

Since a large portion of the ovaries is left in place, there is a residual risk of high-grade serous carcinoma that is probably very low but not zero. It could be due to the degeneration of STIC tissue left in place on the ovary (but which would also exist on the fimbriectomy specimen) or by the degeneration of inclusion cysts [Kurman, 2010]. Finally, the development of any other type 1 tumor can be observed from tissue included in these same cysts or a non-epithelial tumor, germ cell tumor, or sex cords that is not related to the BRCA gene abnormality.

Any abnormal abdominal or gynecological symptoms, whether there is a genetic background or not, should result in appropriate imaging being performed, possibly repeated or supplemented by surgery. The follow-up of these asymptomatic women at risk should also be considered.

Surveillance methods have proved ineffective at screening for high-grade serous carcinoma. However, they make more sense when it comes to detecting a type 1 tumor or a non-epithelial tumor that usually grows more slowly.

To date, the screening combining the annual CA-125 blood test followed-up according to its transvaginal ultrasound result, appears to be the combination that leads to the least "unnecessary" surgeries while detecting most early cancers, as shown in the largest randomized screening study conducted to date [Menon 2009].

For other women without lesions identified on the fimbriectomy specimens, we thus propose to base the pelvic monitoring procedures of these women on this protocol. This gynecological screening will be combined with breast disease screening.

If a test is abnormal, it is repeated. In case of persistent abnormality, further clinical assessment (MRI) or surgical follow-up will be discussed.

| Type of Assessment                                                                                               | Timeline - Comments                                                |
|------------------------------------------------------------------------------------------------------------------|--------------------------------------------------------------------|

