#### **8-6-4 Study withdrawal assessment**

| Type of Assessment                                                                                              | Timeline - Comments                                   |
|-----------------------------------------------------------------------------------------------------------------|-------------------------------------------------------|
| PHYSICAL EXAMINATION
Gynecological examination
Additional examination left to clinician discretion |                                                       |
| LABORATORY TESTS
- FSH, estradiol, inhibin B and anti-Müllerian hormone (ovarian reserve)             | In case of menstrual disorders or menopausal symptoms |
| - CA-125                                                                                                        | Single assay                                          |

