### **8-7 Endpoints**

#### **8-7-1 Pelvic cancer**

The cumulative incidence of pelvic cancer will be estimated by measuring the time-to-onset of pelvic cancer, defined as time from the date of the fimbriectomy to the date of the ovarian cancer, high-grade primary peritoneal cancer, or cancer of other gynecologic pelvic location, with death without pelvic cancer considered a competitive event. Study withdrawal for oophorectomy is also a competitive event. Patients alive without pelvic cancer or oophorectomy based on most recent information are censored at this time.

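### The ovaries removed at secondary oophorectomy have no prescribed pathology and no histology item, so the primary incidence can be understated by an amount that cannot be estimated

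*Protocol*

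**What the plan says.** **First specimen.** Section 9-2 sets the scope: "The tubes and ovarian portions covered by the tube should be studied in their entirety with a more careful study of the fibrial end". Section 9.3.1 adds a slice thickness of 2 to 3 mm where possible, and for the ovary: "Ovarian portions covered by the tube: each ovary fragment is sectioned perpendicular to its longitudinal axis". Section 9.3.2 then fixes the ribbons and stains for those blocks.

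**Second specimen.** Section 9.4.2 covers the surgical route and closes with "They will also be extracted through endoscopic bags". Nothing follows on sectioning or histology.

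**Where the remaining risk lies.** Section 8-6-3 says: "Since a large portion of the ovaries is left in place, there is a residual risk of high-grade serous carcinoma". It calls that risk probably very low but not zero. Section 6-2 presents the later removal of the ovaries as the intended second step, and accepts that some women may decline it.

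**Exit from the study.** Section 8-5 lists as a withdrawal criterion "Post-fimbriectomy oophorectomy (patients will be followed 1 month post-procedure for complications". The withdrawal assessment in 8-6-4 and Appendix 1 consists of an examination, hormone tests, CA-125 and, in Appendix 1, conditional imaging. Section 8-7-4 defines the oophorectomy endpoint by incidence, timing and complications.

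**Primary endpoint.** Section 8-7-1: "Study withdrawal for oophorectomy is also a competitive event".

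**The concern.** The secondary oophorectomy is the one planned occasion on which the retained ovarian tissue can be examined directly. Section 9-2 itself argues that occult lesions, often under 1 mm, are found only by detailed sampling. That standard is applied to the tissue removed first and not to the tissue left at risk.

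Detection of a small lesion in the second specimen therefore depends on the site or outside hospital. The woman leaves follow-up a month later, so there is normally no second chance to count a lesion that was missed. At stake are even ascertainment of the primary event and the direct evidence on whether fimbriectomy leaves disease behind. Section 8-7-2 gives a proportion of occult lesions for the first specimen, but there is no counterpart for the second.

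**Working it through.** **1. The plan's own figure.** Section 8-8-1 says that 8 tumors in 120 patients put the lower one-sided 90% limit above 3%. The observed rate is 8/120 = 6.7%, the exact lower limit is 3.92%, and P(X ≥ 8 | n = 120, p = 0.03) = 0.029. The statement reproduces.

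**2. What is fixed for each specimen.**

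| | Fimbriectomy specimen | Ovaries at secondary oophorectomy |
|---|---|---|
| Sectioning | 9.3.1: slices of 2 to 3 mm | none given |
| Sections and stains | 9.3.2: ribbons of 7, stains named | none given |
| Result as an endpoint | 8-7-2: proportion with occult lesions | none; 8-7-4 has incidence, timing, complications |
| Follow-up afterwards | annual, until menopause | 1 month, for complications |

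**3. Direction of error.** A missed lesion cannot raise the count. The woman has had the competing event and leaves, so the error is downward or nil. The protocol also does not say how a cancer found in that specimen is classified, since its date is that of the competing event. If it were coded as the competing event, better detection would not change the estimate.

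**4. Size, as an illustration only.** Inputs from section 6-1: occult lesions in 2 to 10% of prophylactic adnexal specimens, and 50 to 100% on the tubes. Reading the second figure as a share of lesions leaves 0 to 50% outside the tube. The share having the second operation (f) and the share of lesions missed (m) are not given, so both are assumed.

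- Lesion rate per operation: q = (2 to 10%) × (0 to 50%) = 0 to 5%.
- Lesions present = 120 × f × q: 0 to 3.0 if f = 0.5; 0 to 6.0 if f = 1.
- Lesions missed = present × m. With m = 0.5: 0 to 1.5 (f = 0.5) and 0 to 3.0 (f = 1). With m = 1: 0 to 3.0 and 0 to 6.0.
- In percentage points: 1.5/120 = 1.25; 3.0/120 = 2.5; 6.0/120 = 5.

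**5. What that would mean for the final rule.** Suppose the counted rate is 3% and missed cases bring the true rate to 4.25%, 5.5% or 8%. The chance of reaching 8 of 120 with full detection would be 0.14, 0.34 or 0.75, against 0.03 as counted. This applies to the 3-year rule only for oophorectomies within that window.

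**The case against.** **General wording already covers the second specimen.** Section 9-2 states: "The pathological study of operative specimens should optimize the possibility of detecting early carcinoma". Section 9-3 sends surgical specimens to each site's laboratory. This gives an aim and a route, but no method for a whole residual ovary and nothing for outside hospitals.

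**A cancer found there would be reported.** This stands for a recognised cancer. The letter in Appendix 2 asks about the occurrence of pelvic cancer as well as further pelvic surgery. Section 8-7-5-2 names second cancers as an example of a medically significant event, and 8-7-5-6 asks for serious events during the study (later ones if reasonably related to the research). Pelvic cancer is also the primary endpoint, so its date has to be collected. A reader might infer that findings in the second specimen go unrecorded, and the documents do not support that. What lacks a dedicated item is an in situ lesion, a negative result, and whether the ovaries were examined.

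**The 8-6-4 wording "Additional examination left to clinician discretion" is not about pathology.** Correct. It belongs to the physical-examination row and shows only that the assessment has no histology row.

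**The lesion rates do not transfer.** This stands too. The 2 to 10% comes from specimens that include the tubes and counts in situ lesions, while the primary endpoint is cancer. Here the tubes are already gone, and women with STIC or invasive cancer at fimbriectomy are excluded from the incidence analysis (8-8-2).

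**It belongs in the analysis plan.** It does not. No analysis can recover tissue that was not sectioned or a report that was not requested.

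**Conclusion.** The omission holds, and it concerns ascertainment of the primary event. Detection in the retained ovaries depends on local practice, the result has no dedicated item, and any resulting error favours the procedure.

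Two stronger conclusions are tempting and not supported:

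- **That the primary incidence is understated.** The documents do not give the share of women having the second operation, the lesion rate in ovaries after fimbriectomy, or the yield of routine pathology. The illustrative range starts at zero. What can be said is that the incidence can be understated, by an amount that cannot be estimated.
- **That one missed lesion is a large, known part of the expected count.** At 3%, 120 × 0.03 = 3.6 tumors are expected, so one would be 1/3.6 = 28%. But 3.6 is a 3-year count, whereas the second operation is intended near menopause in a study projected to August 2034. Against the protocol's 10% at 10 years the expected count is 12, and one is 8%. Neither ratio says how many lesions are missed.

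The upper figures in the working rest on assumed values of f and m, on intact-adnexa rates, and on reading the tubal figure as a share. They show why a few cases matter against a threshold of 8; they do not estimate the bias.

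**What to change.** 1. **Record the result.** Add to 8-6-4, Appendix 1 and the Appendix 2 letter: histology report of the secondary oophorectomy (no lesion / in situ / invasive, site, histological type). Obtain it retrospectively for operations already done, and from outside hospitals where available. Report the proportion of specimens examined and the proportion with an occult lesion. Cost: one form item, one line in the letter and report retrieval.
2. **Settle the classification.** State in 8-7-1 that a cancer found in that specimen counts as the pelvic-cancer event and not as the competing event. Cost: one sentence.
3. **Optional.** Apply the 9.3.1 slice thickness to future secondary-oophorectomy specimens at study sites, and describe results by whether it was used. This adds some pathology blocks, does not bind outside hospitals, and changes ascertainment over calendar time because earlier specimens were handled locally. The first two changes stand without it.
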